**Figure 1 figure1:**
[figure not shown]
WorkWell Study timeline.

### Study Eligibility

Potential participants will go through a biphasic screening process to determine eligibility, see full eligibility criteria in Textbox 1. Participants will complete the web-based screening questionnaire, which will be reviewed by staff to determine initial eligibility; individuals who are conditionally eligible will be asked to consent to continue the screening process and to complete a medical history review. Next, an in-laboratory visit will confirm BMI eligibility. Those with qualifying BMIs are considered eligible to participate in the WorkWell Study and will have the opportunity to undergo full informed consent.

Eligibility criteria
**Inclusion criteria**
Age of ≥18 yearsPrimary work activities performed seatedAbility to use sit-stand workstationWorks ≥4 days per week (in-office or remote)BMI of ≥25 (≥23 for Asian descent)
**Exclusion criteria**
Taking certain medications and supplements, which includes glucose control, blood pressure, and blood thinner medications; hormone replacement therapy; corticosteroids; high-dose statins; second-generation antipsychotics; and prebiotics, probiotics, or antibiotics (in previous 3 months)Inability to stand or move for prolonged periods due to lower limb injury, disability, preexisting medical condition, or doctor’s ordersSerious medical conditions including, neuromuscular, cardiovascular, and respiratory disorders, as well as inflammatory bowel or intestinal malabsorption conditions, or food allergiesActively using a sit-stand workstationWork travel of ≥3 days per weekSmoking

### Procedures

#### Study Recruitment

Participants will be recruited on a rolling basis from the Arizona State University community via email listserves, slack channels, e-newsletters, staff website advertisements, and word-of-mouth. Preexisting partner businesses and organizations throughout the Phoenix Metropolitan area will be contacted by email. Employee-facing flyers containing study information and a link to the screening questionnaire will be disseminated electronically through the aforementioned channels.

#### Baseline Period

Once enrolled and initial baseline measures taken, participants will go through a 1-week baseline period in which they are outfitted with multiple devices that they will wear during each intervention period: a continuous glucose monitor (FreeStyle Libre, Abbott Diabetes Care), activPAL micro (PAL Technologies), and GENEActiv accelerometer (ActivInsights). These devices will be worn continuously (ie, 24 hours per day) for 7 consecutive days to assess baseline glycemic response, activities (including sitting, standing, and lying behaviors), and sleep, respectively. Participants will engage in their normal behaviors during the week-long baseline period.

Lunch will be delivered on workdays during the baseline period and both intervention periods. Participants will select options from a standardized menu (approximately 33% of daily caloric needs is equal to 660 kcals, with macronutrient composition of 55% carbohydrate is equal to approximately 90.75 g, 30% fat carbohydrate is equal to approximately 22 g, 15% protein [±10%] is equal to 24.75 g) created from a list of local vendors. The standardized meal choices will be consistently repeated each week during the trial, with the same meals provided Monday to Friday during baseline and both intervention periods. Participants will be asked to avoid eating or drinking (with the exception of water and black coffee or tea) 3 hours before and post lunchtime. Food logs will be used to report when they started and finished eating their lunch, how much food they ate, and the exact food consumed during the trial.

#### Randomization

After completion of the baseline period, each participant will be randomized to an intervention sequence (MOVE-STAND or STAND-MOVE). Randomization is completed using the REDCap (Research Electronic Data Capture; Vanderbilt University) randomization tool and a preloaded table with treatment sequences [32,33].

#### Interventions

The MOVE and STAND interventions will be delivered across 2 work weeks (approximately 10 days). Both use the WorkWell mobile app and Bluetooth Activator micro (PAL Technologies) device as intervention tools in conjunction with the equipment worn during the baseline period (Figure 2). The primary behavioral target of the MOVE intervention will be to increase baseline LPA time by an additional 6 minutes per hour during work. Similarly, the primary behavioral target of the STAND intervention will be to increase baseline standing time by an additional 6 minutes per hour during work. This target of adding 6 minutes per working hour of standing and LPA was selected as an achievable goal with evidence for cardiometabolic health improvements [14-19,22].

After the baseline period is completed, the self-reported work hours and corresponding activPAL micro data will be used to identify the average minutes of standing and moving for each hour of the participant’s workday. The intervention goals will be identified for each participant by adding 6 minutes to these hourly averages. For example, if a participant stands for an average of 10 minutes per work hour during the baseline period, their STAND intervention goal will be 16 minutes of standing per work hour. The same approach will be used to identify MOVE intervention goals. The WorkWell app will use live feedback from the Bluetooth Activator micro to prompt participants in the STAND intervention to meet their hourly standing goals using a sit-stand workstation, while the MOVE intervention will prompt participants to engage in light-intensity movements (eg, walking) to meet their hourly goals.

Prior to the start of the intervention, staff will meet with participants to provide the devices, equipment, and logs needed during the intervention period. Participants will undergo an introductory tour before each intervention and are reminded of their intervention goal for that period. During the intervention, participants will wear the Bluetooth Activator micro device on the mid-thigh and use the WorkWell mobile app during their workday in conjunction with the continuously-worn continuous glucose monitoring (CGM), activPAL, and GENEActiv. When the workday begins, participants will wear the Bluetooth Activator micro and log their work start time in the app, signaling the “start” of the intervention for that day. The Activator micro device will send real time accelerometer data to the WorkWell app via a Bluetooth signal, providing live participant-facing feedback on hourly goal progress as well as day-level summary information. Summary data will also be sent to a secure server, allowing study staff to monitor participant compliance and to facilitate support when needed. Participants will additionally receive a variety of prompts, including hourly reminders to work toward their hourly goal, encouraging messages, or messages that acknowledge that they achieved their hourly goal. Participants will be instructed to log the end of their workday in the app before removing the Bluetooth Activator micro, thus signaling the “end” of that day's intervention.

**Figure 2 figure2:**
[figure not shown]
WorkWell intervention tools—WorkWell mobile app and Activator micro device.

#### Measures

All measurements will be completed at the baseline visit and after each intervention period, for a total of 3 laboratory visits. Table 1 shows the measures collected and the associated measurement period. Demographic and health history information will be assessed at baseline. During the baseline period, as well as during each intervention period, participants will complete 3 paper-form daily logs for sleep, work, and food recall. All other study data and questionnaires will be collected and managed using REDCap hosted at Arizona State University [32,33]. REDCap is a secure, web-based software platform designed to support data capture for research studies, providing (1) an intuitive interface for validated data capture, (2) audit trails for tracking data manipulation and export procedures, (3) automated export procedures for seamless data download to common statistical packages, and (4) procedures for data integration and interoperability with external sources.

**Table 1 table1:** WorkWell measurement schedule.

Measures				Baseline	Intervention 1	Intervention 2
**Screening**						
		Demographics and health history		✓^a^	—^b^	—
		BMI (kg/m^2^)		✓^c^	—	—
**Primary outcomes**						
		Postprandial blood glucose (incremental area under the curve)		✓^d^	✓^d^	✓^d^
**Secondary outcomes**						
		Intervention adherence (% goal met)		✓^d^	✓^d^	✓^d^
		Posture/activity (minutes/day)		✓^d^	✓^d^	✓^d^
**Exploratory outcomes**						
	Sleep			✓^d^	✓^d^	✓^d^
	Intervention feasibility			✓^a^	✓^a^	✓^a^
	**Anthropometrics**					
			Body weight (kg)	✓^c^	✓^c^	✓^c^
			Body fat percentage (%)	✓^c^	✓^c^	✓^c^
			Waist circumference (cm)	✓^c^	✓^c^	✓^c^
	Endothelial function (% flow-mediated dilation)			✓^c^	✓^c^	✓^c^
	Blood pressure (mm Hg)			✓^c^	✓^c^	✓^c^
	**Fasted blood measures**					
			Glucose (mg/dL)	✓^c^	✓^c^	✓^c^
			Insulin (μlU/mL)	✓^c^	✓^c^	✓^c^
			HDL-cholesterol (mg/dL)	✓^c^	✓^c^	✓^c^
			LDL oxidation (U/L)	✓^c^	✓^c^	✓^c^
			Triglycerides (mg/dL)	✓^c^	✓^c^	✓^c^
			Total antioxidant capacity (µmol/L)	✓^c^	✓^c^	✓^c^
	Microbial diversity			✓^c^	✓^c^	✓^c^
	Hemoglobin A_1c_ (mg/dL)			✓^c^	N/A^e^	N/A
	Metabolomics (stool and plasma)			—	—	—
	DNA variants			✓^c^	—	—

^a^Self-administered survey via REDCap (Research Electronic Data Capture).

^b^Not measured.

^c^Measured at each laboratory visit.

^d^Measured continuously (device-based).

^e^N/A: not applicable.

#### Primary Outcomes

Our primary outcome, the change in 3-hour postlunch postprandial glucose excursion, will be assessed using a CGM device. This small, single-use sensor is placed on the back of the arm and samples glucose levels approximately once every 15 minutes for up to 14 days [34]. This device provides a valid and reliable measure of glucose using flash glucose monitoring [35,36]. Research staff will facilitate the insertion of the CGM for baseline and both intervention periods. If the device falls off or is accidentally removed, staff will replace the device as needed. Participants will be provided a macronutrient-controlled meal (approximately 33% of daily caloric needs, with macronutrient composition of 55% carbohydrate, 30% fat, 15% protein [±10%]) delivered daily for lunch during the work week to control for dietary variability. The 3-hour postlunch postprandial incremental area under the curve (iAUC) and mean blood glucose concentration in response to the lunchtime meal will be calculated from these data.

#### Secondary Outcomes

The secondary outcomes of the interventions will assess intervention adherence and changes in sitting, standing, and LPA during work hours. Intervention adherence is defined as meeting the hourly intervention goal of ≥80% of the workday (eg, meeting the hourly goal for ≥8 hours during a 10-hour workday). The Activator micro device will be taped midthigh during work hours and will communicate with the WorkWell smartphone app via Bluetooth technology. The app’s user-friendly interface will provide real time feedback, allowing participants to monitor their progress as 8 bubbles gradually turn green to signify the hourly goals that were met. The WorkWell app will sync to a secure server, providing real time stand-and-move data for study staff to monitor adherence to intervention protocols; data will be stored for broader analysis upon trial conclusion.

The activPAL micro will also assess sitting, standing, and moving behaviors. Work logs will be used to differentiate between work and nonwork hours. Device attachment procedures are based on several large-scale intervention studies [5,6,37]. Devices will be waterproofed using a medical grade adhesive covering and placed on the midline of the thigh with breathable, hypoallergenic tape, to allow for 24 hours per day of continuous wear during measurement periods without removing for bathing or other water-based activities. Data will be processed into bouts of sitting or lying, standing, stepping, or time in bed (ie, primary lying bout) and expressed as minutes per day, assessing posture and intensity using activPAL software version 8.10. Waking time assessed as lying or seated will be categorized as sedentary behavior. Stepping time will be split into periods of LPA (<100 steps per minute) and MVPA (≥100 steps per minute) [38]. Total physical activity will be a cumulative daily value of LPA and MVPA. The following periods of wear will be excluded: (1) continuous sitting or standing behavior >6 hours (considered nonwear), (2) days with ≤10 hours of valid wear time during the wake period, and (3) participants with only 1 valid day of activPAL wear.

#### Exploratory Outcomes

Additional exploratory outcomes will include sleep, intervention acceptability and satisfaction, body anthropometrics, femoral artery flow-mediated dilation (f-FMD), central aortic blood pressure, fasting glucose, fasting insulin, HDL, LDL, LDL oxidation, triglycerides, TAC, gut microbial diversity, HbA_1c_, metabolomics of the blood and stool, and genetic variants assessed during 1 or more measurement periods.

Sleep will be assessed using the wrist-worn GENEActiv accelerometer (ActivInsights) (initialized to collect at 40 Hz); participants will wear the device 24 hours per day during the measurement periods while also completing a validated sleep diary each night to identify sleep from wake periods. The GENEActiv device has been validated for sleep [39-42] and will be used in conjunction with a sleep log that differentiates sleep or wake periods in data [43]. An open-source and validated algorithm (GGIR package, R-software) [42] will be used to process device-based sleep measures, including sleep duration, sleep efficiency, sleep onset latency, and wakefulness after sleep onset [44-47]. Sleep will be considered the total sleep time accumulated within the sleep window; wake time, daytime sleep, and the time of sleep onset will not be counted. GGIR signal processing includes autocalibration using local gravity as a reference [45], detection of prolonged abnormal high values, nonwear detection and average magnitude of dynamic acceleration calculation, corrected for average gravity over 5-second epochs and reported in milligravitational units (mg). Data files will be excluded if a postcalibration error of >0.01 g (10 mg), <3 days of valid wear (defined as >16 hours per day [44,48]), or wear data are not present for each 15 minutes period of the 24-hour cycle. Nonwear detection is described elsewhere [44]. The default nonwear setting will be used, which includes invalid data that will be imputed by the average at similar time points on different days during the assessment week. Sleep duration will be calculated using automated sleep detection (HDCZA sleep detection algorithm) [47]. The average of all valid days will be used.

Intervention acceptability and satisfaction will be assessed using the Treatment Evaluation Questionnaire (TEQ) to measure the adherence and feasibility outcomes of the study. Prior to starting each intervention, participants will be provided an introductory tour to explain the intervention and describe how to use the WorkWell app and device. Research staff will actively discuss strategies to assist participants in engaging with the intervention. After this session and prior to the start of the intervention, participants will be sent a pre-study survey with the TEQ; once each intervention is completed, a postsurvey is sent also containing the TEQ.

Body anthropometrics, including height, weight, body fat percentage, and waist circumference, will be measured at each laboratory visit. Height and weight will be measured using the Seca scale and stadiometer (Seca 286 EMR Ready Ultrasonic Measuring Station). Waist circumference (taken at the level of the iliac crest) will be measured twice using a Gulick tape measure. Body fat percentage will be measured twice using the Tanita TBF-400 digital scale device (Tanita), which calculates percent body fat using bioimpedance. If there is a difference of ≥0.2% for body fat, an additional measurement will be taken. Values will be averaged to arrive at a final measure.

f-FMD will be used to measure the endothelium-dependent, flow-mediated dilation of the superficial femoral artery using B-mode ultrasound (Terason uSmart 3300+TM) via guidelines set forth by the Brachial Artery Reactivity Task Force [49]. Participants will be asked to lie quietly for 15 minutes on the ultrasound table before baseline images are obtained from their left upper thigh. Simultaneous ultrasound images (B-mode) and Doppler waveforms will be recorded for 30 seconds. An appropriately sized cuff will be selected based on manufacturer guidelines (Hokanson Instruments) and subsequently wrapped around the participant’s upper thigh, 3-4 cm below the bifurcation of the common femoral artery. After baseline images of the superficial femoral artery are acquired, the blood pressure cuff on the participant’s upper thigh will be inflated using a rapid-cuff inflator (Hokanson instruments) to a suprasystolic pressure of 250 mm Hg for 5 minutes. The recording of the image will begin 30 seconds prior to the cuff release. At 5 minutes following cuff inflation, the cuff will be rapidly deflated and arterial images are recorded for 6 minutes. Images obtained will be analyzed by a trained, blinded researcher using previously validated edge-detection software [50]. In our laboratory, intraclass correlation coefficients for baseline and peak diameter are 0.994 and 0.995, respectively (Cronbach α=.976).

Central aortic blood pressure that includes both central and peripheral blood pressure, and aortic stiffness (via applanation tonometry) will be measured using the SphygmoCor XCEL (CvMS; ATCOR Medical). This device has been found to reflect measures of central pressures and stiffness reliably and accurately [51,52]. All measurements will be taken after the participant rests in a supine position for approximately 15 minutes, prior to f-FMD initiation, to ensure hemodynamic stability. Triplicate measures will be collected, and the 2 closest values averaged and reported.

Fasting blood samples will be collected at each laboratory visit via venipuncture. The 15-mL samples will be immediately processed and aliquoted for storage at –80 °C for subsequent analysis. Fasting blood glucose will be examined in multiple batches, pairing samples from the same participant’s previously aliquoted plasma. Plasma glucose concentration will be analyzed using the AU480 Chemistry Analyzer (Beckman Coulter, Inc) in accordance with manufacturer’s instructions. Exploratory cardiometabolic disease risk analysis will be performed on plasma and serum glucose, insulin, triglycerides, total cholesterol, HDL cholesterol, LDL cholesterol, LDL oxidation, and TAC. Exploratory, targeted metabolomics analyses will also be performed with plasma samples using mass spectrometry (MS).

Participants will be provided with a stool sample collection kit and instructions at each laboratory visit. All participants will be given the option to schedule sample pick-up at their home or workplace; alternatively, samples can be dropped off at the Translational Research Center. Participants will be instructed to collect this sample within 4 days of each laboratory visit for a total of 3 collections. Once collected, samples will be frozen at –80 °C within 24 hours of the sample leaving the body. Participants will be instructed to contact staff to retrieve the sample when ready. The stool samples will later be thawed at 4 °C and microbial DNA extracted for microbiome sequencing and characterization of intervention-specific bacterial community differences. Microbial DNA sequencing will be carried out in batches of paired samples from the same participant. Bacterial DNA will be extracted from the stool samples using DNeasy PowerSoil Pro DNA Isolation Kit (47014, Qiagen) as per manufacturer recommendations. DNA quality and concentration will be quantified (QIAxpert System Qiagen) before being sent out for sequencing (Illumina MiSeq instrument, Illumina, Inc.) at ASU’s DNASU Genomics Core Facility. Raw Illumina microbial data will be cleaned and analyzed using the Quantitative Insights into Microbial Ecology 2 software, as previously described [53]. Exploratory, targeted metabolomics analyses will be performed with the stool samples using MS. Short-chain fatty acids, bile acids, pathway-specific targeted liquid chromatography tandem MS, liquid chromatography–MS, gas chromatography–MS aqueous metabolite profiling, and liquid chromatography–MS global lipidomic profiling will be carried out.

HbA_1c_ will be collected at baseline only using the DCA Vantage analyzer (Siemens Munich) with 1 μL of blood obtained using a finger stick. After collection, the results are obtained within 6 minutes and data will be used for descriptive purposes.

Saliva samples will be collected at baseline using Oragene Discover collection kits (OGR-600 Ottawa), and will be archived for future exploration of genetic variants.

### Data Analysis

#### Statistical Analysis Plan

Participant characteristics will be reported as frequencies or means with SDs. Outcome variables with nonnormal distributions will be log-transformed to assume normal distribution. All data processing and statistical analyses will be performed in SAS (version 9.4; SAS Institute) with an α criterion of .05. To address our specific aims and hypotheses, we will use linear mixed model analyses [54,55] for intervention (ie, MOVE and STAND), sequence (ie, MS and SM), and time period (ie, 1 or 2) as fixed factors and an unstructured covariance structure for the 3 repeated measurements per person. The primary outcome will be postprandial glucose iAUC, and secondary outcome will be change in posture and LPA. All data from randomized participants will be included in the analyses in accordance with intent-to-treat principles.

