## Methods

### Study Aims

The primary aim of this study is to examine the impact of 2 different intervention conditions (STAND and MOVE) on 3-hour postlunch postprandial glucose compared to the baseline control condition. Interventions entail adding 6 minutes per hour to baseline standing and LPA minutes during the workday. We hypothesize that both intervention conditions will improve postprandial glucose regulation. The secondary aim is to assess intervention adherence and changes in standing and LPA. Exploratory aims include (1) assessing participant acceptability and satisfaction during the intervention; and assessing intervention-induced changes in (2) sleep, (3) anthropometrics and body composition, (4) endothelial function, (5) central and peripheral blood pressure, (6) fasting blood glucose concentration, (7) fasting insulin concentration, (8) fasting high-density lipoprotein (HDL) concentration, (9) low-density lipoprotein (LDL) oxidation, (10) fasting triglycerides, (11) total antioxidant capacity (TAC), (12) hemoglobin A_1c_ (HbA_1c_), (13) microbial diversity of the gut, (14) metabolomics from stool and plasma, and (15) DNA variants that may explain differences in response to the intervention.

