### Study Design

The WorkWell Study is a pilot 6-week randomized crossover design with 2 balanced arms. Across 2 intervention periods, all participants (N=15) will experience both workplace interventions following a baseline control condition: (1) MOVE, an intervention targeting 6-minute increase in baseline LPA each work hour and (2) STAND, an intervention targeting 6-minute increase in baseline standing each work hour via a sit-stand workstation. Participants will wear a Bluetooth accelerometer and will be prompted with a mobile app during each intervention period. The intervention sequence is randomized and a washout period of at least 1 week will occur between interventions to reduce any potential carryover effect. Clinic-based assessments will occur at baseline and after each intervention period is completed (Figure 1).

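### As written for iAUC, the stated mixed model gives baseline no factor level, so it yields MOVE versus STAND but not the primary contrast of each intervention with baseline

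*Protocol article*

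**What the plan says.** All references are to the Protocol article.

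- **Study Aims:** the primary aim is the effect of STAND and of MOVE "on 3-hour postlunch postprandial glucose compared to the baseline control condition". The Sample Size Calculation is likewise built on a difference between baseline and the two intervention measurements.
- **Statistical Analysis Plan:** one model serves all of this: "To address our specific aims and hypotheses, we will use linear mixed model analyses". Its terms are "intervention (ie, MOVE and STAND), sequence (ie, MS and SM), and time period (ie, 1 or 2) as fixed factors", with "an unstructured covariance structure for the 3 repeated measurements per person". The outcome is named without reference to change: "The primary outcome will be postprandial glucose iAUC". In the same sentence, change is used only for the secondary outcome.
- **Primary Outcomes:** the outcome is worded differently: "Our primary outcome, the change in 3-hour postlunch postprandial glucose excursion, will be assessed using a CGM device".
- **Study Design:** participants "will experience both workplace interventions following a baseline control condition". Under Randomization, only the order of MOVE and STAND is randomized, after the baseline period.

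**The concern.** The *ie* in the model sentence makes both lists of levels complete: two interventions and two periods. These describe the two intervention records of each person and leave no value for the baseline record. Yet the covariance clause counts three measurements, so baseline is evidently meant to be a response. The sentence conflicts with itself and with the primary aim.

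This is the only analysis stated for the primary hypothesis. More than one model can be read into the wording, and as long as it stands the choice between them is open to being made after the data are seen. One of those readings does not contain the primary comparison at all.

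**Working it through.** The plan gives no figure on this point to reproduce. The check is whether the primary contrast is estimable under each reading. A contrast L is estimable when L = L(X⁻X), where X is the fixed-effects design matrix and X⁻ a generalised inverse.

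**Inputs.** Two sequences (MS, SM) and three occasions (baseline, period 1, period 2) give 2 × 3 = 6 cells.

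| Sequence | Occasion | Intervention level listed | Period level listed |
|---|---|---|---|
| MS | baseline | none | none |
| MS | first intervention | MOVE | 1 |
| MS | second intervention | STAND | 2 |
| SM | baseline | none | none |
| SM | first intervention | STAND | 1 |
| SM | second intervention | MOVE | 2 |

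**1. iAUC with the factors as listed.** Four of the 6 cells have levels. Columns: 1 intercept + 2 interventions + 2 sequences + 2 periods = 7; rank 4. MOVE minus STAND is estimable. No parameter refers to baseline, so neither primary contrast can be written.

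**2. Change from baseline with the factors as listed.** The matrix is the same, but the response is now the period value minus baseline. The adjusted mean change for STAND (intercept + STAND + ½ of each sequence term + ½ of each period term) is estimable, and by symmetry so is that for MOVE. Tested against zero, these are the primary contrasts. The number of measurements is then 3 − 1 = 2 per person.

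**3. iAUC with a three-level condition factor, and period scored 0 at baseline, −½ in period 1 and +½ in period 2.** All 6 cells enter; rank 5. STAND minus baseline and MOVE minus baseline are both estimable.

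**4. iAUC with three levels in both condition and period.** Columns: 1 + 3 + 2 + 3 = 9; rank 5. The baseline column and the period-0 column are identical. Adding c to the baseline effect and subtracting c from the period-0 effect changes no fitted mean, but it shifts the bare row MOVE minus baseline by −c, so that row is not estimable. With period coefficients (−1, ½, ½) attached, the shift is −c + c = 0 and the contrast is estimable. Readings 3 and 4 span the same column space (rank 5 each, rank 5 joined). They are the same fitted model, and only the contrast row differs.

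**5. What the contrast with baseline takes in.** Illustration, with an assumed drift of −5 units per occasion, an arbitrary start of 100 and no true effect: the means are 100, 95 and 90. Under reading 3, STAND averages (90 + 95)/2 = 92.5 and MOVE averages (95 + 90)/2 = 92.5. Each contrast with baseline is 92.5 − 100 = −7.5, while MOVE minus STAND is 0.

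**The case against.** The strongest reply is that the outcome is a change score, as Primary Outcomes says. The two-level factors are then the ordinary crossover factors and the primary contrast is estimable (reading 2). That is correct, and it limits the point. It does not rescue the text: it contradicts the three measurements, and the analysis section names iAUC while reserving change for the secondary outcome.

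A second reply is that baseline is an unlisted third level of intervention. This is probably what was intended. But the listed levels exclude it, and the period value at baseline is left undefined, which determines how the primary contrast must be written.

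A third is that a condensed article leaves such detail to a fuller plan. That holds for the scoring of period and for degrees of freedom, and their absence is not criticised here. The factor levels and the number of measurements, however, are stated, and they do not fit together.

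A reader might also infer more than the documents support:

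- That no comparison with baseline is possible. The data collected do allow one.
- That adding a baseline level to both factors fails outright. It is the same fitted model as reading 3 and needs only a correctly written contrast.
- That the software would discard the baseline rows. The article names SAS 9.4 but neither a procedure nor a data coding, so this cannot be known.

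**Conclusion.** Wrong as written, and correctable. On the named outcome, iAUC, the stated model covers 4 of 6 sequence-by-occasion cells, which is 2 of the 3 measurements per person, and contains MOVE versus STAND but neither contrast with baseline. On the change-score reading the contrasts exist, but the stated count of three measurements is wrong. Neither reading fits all the text. The conclusion rests on taking the listed levels as complete, as *ie* implies, and does not depend on any numerical assumption about the data.

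One limit remains under every version. Baseline always comes first and is not randomized, so the contrast with baseline includes any time trend between baseline and the intervention periods. No recoding removes this. It has to be stated as an assumption.

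**What to change.** Choose one model and word the Statistical Analysis Plan and Primary Outcomes sections to match it.

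- **(a) iAUC at three occasions.** Use a three-level condition factor (baseline, STAND, MOVE), sequence, and a period effect confined to the two intervention periods, for example scored 0, −½, +½. If a three-level period factor is preferred, the contrast must average the period 1 and 2 terms and subtract the baseline-period term. The unstructured covariance for three measurements then stands.
- **(b) Change from baseline.** Keep the two-level factors, state 2 measurements per person, and test each intervention's adjusted mean change against zero.

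The two are not the same model: (a) fits 5 free means to 6 cells, whereas (b) fits 4 to 4 change cells. They need not return identical estimates, so one should be fixed in advance.

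Under either, name STAND minus baseline and MOVE minus baseline as the primary contrasts, and state the assumption of no time trend from baseline to the intervention periods.

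The cost is one paragraph of analysis text and a few lines of code. Data collection, randomization and conduct are unchanged.
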